PRO measures direct patients to report on their experience and therefore supply unique data for the management of RA. Because PROs are reported directly by patients on paper or electronic questionnaires, they reflect how a patient feels and functions in relation to RA and its therapy [4,5]. Although PRO measures necessitate patient attention and effort, they are also useful for understanding a patient’s subjective experiences. They can help to facilitate clinician-patient communication and shared decision-making to improve the quality of patients’ care, and they can help to identify both common and divergent perceptions of disease activity and treatment effectiveness between clinician and patient. While the advent of smartphone technology has enabled convenient and remote capturing of electronic PRO measures (ePROs) between in-person clinician visits [6,7], a patient must still recall their symptoms over a day- or week-long period. In the quest for additional patient-generated data to complement patients’ reported experiences of physical function, pain, sleep, fatigue, and so on, biometric sensors may play an important role in providing continuously captured objective data (ie, activity, heart rate and sleep hours).

To date, there are few published studies investigating the extent to which biometric data correspond with RA patients’ subjective reports of their symptoms and disease activity. Performance outcome measures (eg, gait, distance traveled, and acceleration) collected passively using smartphone applications have been found to be associated with RA symptoms in studies with small samples ranging from 20-80 participants [8,9]. A recent proof of concept, human factors study explored the experience of 15 subjects who wore an activity tracker daily over 1 week and completed ePRO questions about stiffness, sleep quality, and joint pain in the morning and evening. The investigators reported that initial analyses showed modest correlation between the duration of morning stiffness reported in the ePRO and the level of morning activity tracked by the activity tracker. These investigators are planning a larger trial in a clinical setting with RA subjects receiving medication [10].

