#### Lead-In Period

Prior to receiving their smartwatch, invited participants will successfully complete a 14-day lead-in period during which they are required to meet the following inclusion criteria: (1) complete two daily ePRO measures, specifically the single-item Pain and Fatigue numeric rating scales (NRS), on at least 10 of the 14 days; and (2) complete two weekly core sets of ePRO measures (Table 1), over the 14-day period. Those who do not meet these requirements will be offered a single opportunity to repeat the lead-in period and subsequently qualify for the remainder of the DIGITAL study. This initial phase will serve to acclimate participants to regular data collection and provide some assurance that they are willing and able to take part in and complete study requirements over the 3-month main study period.

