**Passively collected biosensor data (continuous [if smartwatch is synced every <5 days]/Fitabase)**			
	Activity	Steps (minute, hour, day) Activity intensity (minute, hour, day) Distance (day) - units = miles Energy expenditure (minute, hour, day) Metabolic Equivalents (minute)	
	Activity-derived variables	Time walking per day (minutes) Time in activity intensity categories per day (minutes) Active time (minutes) Aerobic time (minutes)	
	Heart rate	Beats per minute (minute, day)	
	Heart rate–derived variables	Time in heart rate zone of interest based on exercise charts	
	Sleep	Time sleeping in last 24 hours (minute, day)	
	Sleep-derived variables	Time in light, deep, and REM^i^ sleep and time to sleep onset, time awake and other derived variables (day)	
	Adherence to wearing and syncing smartwatch	Ratio of days with smartwatch data to number of days during study period prior to discontinuation or end of study period	
	Persistence with wearing and syncing smartwatch	Days until first day without any smartwatch data in Fitabase	

^a^RTA: refuse to answer.

^b^RA: rheumatoid arthritis.

^c^Not applicable.

^d^DMARD: Disease-Modifying Antirheumatic Drug.

^e^ePRO: electronic patient-reported outcome.

^f^NRS: numeric rating scale.

^g^PROMIS-CAT: Patient-reported outcome measurement information system-computer adaptive testing.

^h^OMERACT: Outcome Measures in Rheumatology.

^i^REM: rapid eye movement.

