### Analyses

#### Primary Analyses: Agreement Between ePRO and Passively Collected Digital Measures

The primary objective of this study is to quantify the agreement between passively collected digital measures (eg, activity) and ePRO data (eg, pain NRS scores). Descriptive statistics will summarize the demographics and baseline characteristics for all enrolled participants. The primary analysis will be a descriptive summary of the correlation between passively collected biosensor data and ePRO data. See Table 1 for a list of the ePRO and passively collected digital measures. For ePROs assessed weekly, multiple summary measures of the passive measures will be created over the corresponding weekly timeframe. Summaries to be explored include the average over the time period, trends, most recent, minimum, maximum, variation, and transformations in the data. Correlations between the ePRO and passive measures will be quantified using both a simple correlation matrix for each week as well as using repeated measures models over the entire study. Repeated measures models will be implemented using each ePRO as the outcome measure, with time (eg, week as a classification factor), baseline measures, and the various passive measures as potential factors in the model. The starting model will be a simple main effects model, and then a penalized regression model will also be used to optimize model selection, including the potential for 2-way interactions (including with time). This will allow for assessment of changes in correlations over time adjusted for participant level covariates.

For digital measures obtained daily, a repeated measures model will assess the association between the ePRO (outcome) and passive measures over time (with day as the time period of assessment rather than week). Daily ePRO data may lag by a day if it is observed that most participants are responding in the morning. Due to the large number of days in the study, time will be considered a numeric variable in this model.

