Second, acceptable wear patterns must be established in advance to determine which downloaded device data actually indicate a participant’s use of the device for analytical purposes. The unit of measurement and associated time boundaries for analysis must be defined and described in the statistical analysis plans or programming requirements. For this study, we agreed that at least one minute of activity or data in a given hour would indicate that the participant’s data could be used for analysis. Comparison of continuous, minute-level data with data received only once daily or weekly makes the time cut-offs even more important and influential on results when lining up the data. Although tempting to seek strong correlations and good fitting models, there is substantial value in uncovering differences between passive real-time data and periodic ePRO measures. The increased variability and periodic divergence may lead to lower correlations, but they are also the reason multimodal assessment and an associated understanding of the different data streams is critical.

Finally, from a generalizability perspective, passive data collection requires participants that have a level of comfort with technology. The PARADE study observed that participants tended to have more years of formal education and be younger than the nationally representative cohort used for comparison [15]. Thus, research populations employing such technology represent a subsample that may not adequately represent important segments of patients with the disease in question.

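### The one-day lag for daily pain and fatigue scores hinges on a study-wide majority rather than each answer's own time; a single setting would attenuate day-level associations

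*Protocol article*

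**What the plan says.** The Primary Analyses section describes a repeated measures model for daily data, with the ePRO as outcome and the passive measures as factors, "with day as the time period of assessment rather than week". On pairing answers with watch data it says: "Daily ePRO data may lag by a day if it is observed that most participants are responding in the morning".

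The daily ePROs are identified under Lead-In Period, where participants must "complete two daily ePRO measures, specifically the single-item Pain and Fatigue numeric rating scales (NRS") on at least 10 of 14 days. Table 1 gives the anchors of both scales but no recall period and no time of day for answering. The Introduction says only in general terms that "a patient must still recall their symptoms over a day- or week-long period".

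Table 1 lists steps, activity intensity, energy expenditure, heart rate and time asleep at minute level. Distance and the sleep-derived variables (stages, onset, time awake) are listed by day only.

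The Discussion says that comparing minute-level data with daily or weekly answers "makes the time cut-offs even more important and influential on results when lining up the data". It also says: "The unit of measurement and associated time boundaries for analysis must be defined and described in the statistical analysis plans or programming requirements".

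**The concern.** A trigger that depends on the behaviour of most participants has two outcomes: shift the daily ePRO series by a day, or leave it. Each suits one answering habit and not the other. With the shift, an evening answer meets the previous day's activity instead of the day just lived. Without it, a morning answer meets a day that has barely begun.

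Mixed answering times are plausible. The Figure 4 legend says participants are told how long the assessments take so that they can start when ready, and Table 1 collects typical work and sleep schedules.

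One shift may also not suit every watch measure. For a morning answer the relevant activity is probably yesterday's, but the relevant sleep is the night just ended. Depending on how a night is dated, a one-day shift could move sleep to the wrong night for the very majority it is meant to serve.

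At stake is the size of the correlations that the study sets out to quantify. Mispairing pulls them towards zero and could make a watch measure look like a poorer proxy for daily symptoms than it is.

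**Working it through.** **The plan's own figure.** The only power statement (Sample Size and Statistical Methods) is 250 participants, 75% evaluable, at least 80% power for r = 0.2 and over 90% for r = 0.3 at any given time point. By Fisher z, power = Φ(atanh(r)·√(n−3) − 1.96), with n = 187 to 188 (0.75 × 250 = 187.5) and a two-sided 5% level, which is assumed because no level is stated:

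- r = 0.2: 0.785 to 0.787
- r = 0.3: 0.987 to 0.988

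The stated figures are reproduced to within two points. They concern a correlation across participants at one time point and do not address the lag. The attenuation below is therefore not converted into power.

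**Inputs for the lag.** The document gives neither of the two quantities needed, so both are shown as ranges:

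- m, the share of answers that do not fit the setting used: 10%, 30%, 49%. If the shift follows the majority, m counted over answers stays roughly below one half.
- phi, the lag-1 within-person autocorrelation of the watch measure: 0 to 0.7.

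**Formula.** Suppose an answer has correlation r with its relevant day and is linked to the adjacent day only through autocorrelation. A correctly paired answer then contributes r and a mispaired one r·phi, so

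observed r = r × [(1−m) + m·phi].

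**Results for a true within-person r of 0.30:**

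| m | phi = 0 | phi = 0.7 |
|---|---|---|
| 10% | 0.30 × 0.900 = 0.270 | 0.30 × 0.970 = 0.291 |
| 30% | 0.30 × 0.700 = 0.210 | 0.30 × 0.910 = 0.273 |
| 49% | 0.30 × 0.510 = 0.153 | 0.30 × 0.853 = 0.256 |

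For a true r of 0.20 the same factors give 0.18–0.19, 0.14–0.18 and 0.10–0.17.

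**Check by simulation.** The simulation used 2,000 simulated participants over 84 days, true r = 0.30, and 40% of answers given in the evening:

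| Alignment | phi = 0.3: formula / simulated | phi = 0.5: formula / simulated |
|---|---|---|
| Global one-day lag (m = 0.4) | 0.216 / 0.215 | 0.240 / 0.241 |
| No lag (m = 0.6) | 0.174 / 0.174 | 0.210 / 0.211 |
| By each answer's own time | 0.300 / 0.300 | 0.300 / 0.303 |

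Both global settings lose part of the association, and alignment by answer time recovers it. The no-lag row matters because the text makes the shift optional even when most participants answer in the morning.

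**The case against.** The strongest reply is that the article is a condensed account, the SAP is not shown, and the Discussion assigns time boundaries to the SAP or programming requirements. An absent alignment window would then be no finding. That protects whatever the article leaves unsaid. It does not protect what the article says: on this point it states a criterion, and that criterion is a majority across participants. The SAP may already have replaced it; if so, the point is closed.

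Other objections stand, and they limit the point:

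- A reader might infer that the lag will be imposed on everyone. The text says only that data may lag, and it sets no scope. The harm is conditional on one global setting being used.
- A reader might infer that unlagged morning answers reverse cause and effect. The primary analysis is a descriptive correlation that claims no direction, and morning pain followed by that day's activity is still informative.
- A reader might infer that the rule lets the analyst pick the lag with the better result. The trigger is when people answer, not the observed association. Response timing could also be seen early, since data from 17 pilot participants had already been examined and an interim analysis follows the pilot cohort's first 4 weeks.
- The recall period of the daily items is not stated, so which day is the relevant one is itself partly an assumption.
- The plan does not restrict its correlations to within-person ones. A one-day shift hardly changes differences between participants.
- Re-windowing every measure to the 24 hours before an answer is not possible, because distance and sleep stages are listed only by day.

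**Conclusion.** The point holds in conditional form. The article ties the alignment of daily pain and fatigue scores to a study-wide majority, and if that is carried out as one global setting, off-pattern answers are paired with a less relevant day. The result is attenuation of the day-level within-person association, not its loss.

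The size cannot be fixed from the document. It is slight if about one answer in ten is off-pattern. It can approach a halving only if answering times are almost evenly split and the watch measure has no day-to-day persistence. That extreme should not be read as the expected case.

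The figures assume that the answer relates to one day, that there is no direct link with the adjacent day, and that the association is purely within-person. Relaxing the last two would generally make the loss smaller. The change is worth making because a better rule is available from data the study already collects, but the point does not threaten the study as a whole.

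**What to change.** Replace the majority trigger with an alignment rule based on each answer's own time, fixed before the daily data are analysed:

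1. **Minute-level measures** (steps, activity intensity, energy expenditure, heart rate, time asleep): summarise over a fixed window ending at the answer, of a length consistent with the item's recall period, which should be stated.
2. **Day-level measures** (distance, sleep stages and related variables): assign the calendar day per answer. Morning answers go to the previous day's activity, later answers to the same day's, and sleep always to the most recent night. The plan should give the clock time that separates morning from later answers.
3. **Sensitivity analyses:** report the calendar-day models with and without a global one-day lag.
4. **Description:** report the distribution of answer times, so that readers can judge how much the alignment matters.

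The cost is programming. The current rule already presumes that answer times can be observed, and the minute-level data are already being collected. The small drawback is that windows tied to the answer overlap when an evening answer is followed by a morning one, and leave gaps in the reverse order. The plan should say how these are handled.

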#### Secondary Analyses

Test-retest reliability will be assessed by examining the correlations between each derived digital measure during time periods when observed values of the related ePROs are stable. This includes, for example, assessing the intraparticipant correlations between weekly averaged daily step counts (or associated derived variables) on weeks when participants report the same level of activity as assessed using the Godin Leisure Time Physical Activity Questionnaire [19].

Random forests, gradient boosting, and penalized regression models incorporating cross-validation will be built for detection and prediction of ePRO defined events (eg, flare, adherence, score changes). Baseline and time-varying factors (ie, ePRO, digital measures, and changes in previous time periods) will be included as potential factors in the analyses. Operating characteristics of models will be compared.

Using the Outcome Measures in Rheumatology (OMERACT) flare PRO [20], a question was added after Q7 (“Are you having a flare now?), “If yes, how long ago did it start?” Possible responses included, “I’m not having a flare at this time, Today, Yesterday, 2 days ago, 3 days ago, 4 days ago, 5 days ago, 6 days ago, 7 or more days ago,” so that this study could define the onset date of any RA flare. Descriptive statistics will summarize the trends in the daily ePRO and passive data over the last 3 days prior to the onset of the flare. To assess whether digital measures can accurately classify participants as having an RA flare or not, Classification and Regression Trees and penalized regression incorporating cross-validation will be used.

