Our exploratory study will expand on these prior studies and examine a larger RA population, incorporating digital measures from a Fitbit Versa smartwatch (chosen based on the type of biometric data captured, water resistance and cost) to assess the value of passively collected digital measures as proxies for RA disease activity and other domains of health that may be affected by RA, as reflected in ePROs. Our study differs from PARADE in the use of smartwatch technology and in the manner of participant recruitment. The PARADE study developed a set of wrist activities to measure range of motion [15], but the activity measurement in our study will be passively collected with the smartwatch. Although less sensitive measures are available via the smartwatch, the ability to collect some measure of activity without requiring participant input is an advantage. In addition, PARADE used a broader approach to identify participants in the United States via targeted digital marketing on social media platforms including Facebook, Twitter, and HealthUnlocked. They also made study information available to Facebook users who followed CreakyJoints. In contrast, our study will enroll patients exclusively from members of ArthritisPower, a CreakyJoints-affiliated research registry in the United States. We believe working within an existing population that is already oriented to sharing ePROs will result in greater participant retention. Unlike PARADE, there will be no randomization into groups based on data sharing with the participant during our study, as all participants will be able to view the same amount of their own data throughout. Additionally, PARADE was conducted entirely via app, with no financial incentives and human interaction. In our study, participants will receive compensation based on specific milestones, and members of the research team will monitor their data in real time and, under certain criteria, contact participants when missing data patterns suggest nonadherence to protocol or difficulty in using the technology. Real-time data monitoring offers the opportunity to clarify protocol procedures directly with individual participants.

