### Sample Size and Statistical Methods

We aim to recruit 250 participants who have successfully completed the lead-in period and received the smartwatch to wear for the duration of their participation in the main study and lead-out periods. Assuming at least 75% of the participants complete the majority of the measures, a sample size of 250 will provide at least 80% power to detect correlations between passively collected data via the smartwatch and the actively collected data from ePRO instruments of at least 0.2 and over 90% power to detect correlations of at least 0.3 at any given time point. The analyses will not include any adjustment for multiplicity.

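### Models for ePRO-defined flare and score changes pool ePROs with digital measures as predictors, so their performance alone cannot show what the smartwatch contributes

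*Protocol article*

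**What the plan says.** The Secondary Analyses section of the protocol article plans random forests, gradient boosting and penalized regression with cross-validation. They "will be built for detection and prediction of ePRO defined events (eg, flare, adherence, score changes". On predictors it states: "Baseline and time-varying factors (ie, ePRO, digital measures, and changes in previous time periods) will be included as potential factors in the analyses". On comparison it says only: "Operating characteristics of models will be compared". It does not say which models or predictor sets are meant.

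A later paragraph of the same section plans a separate flare analysis: "To assess whether digital measures can accurately classify participants as having an RA flare or not, Classification and Regression Trees and penalized regression", again with cross-validation. No ePRO predictor is listed there.

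The primary analysis section puts the ePRO on the outcome side: "Repeated measures models will be implemented using each ePRO as the outcome measure, with time (eg, week as a classification factor), baseline measures" and the passive measures as factors. No concurrent or earlier ePRO is listed, apart from whatever counts as a baseline measure.

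On purpose, the Introduction says that the study is "to assess the value of passively collected digital measures as proxies for RA disease activity" and other health domains reflected in ePROs. The Discussion hopes to learn when ePROs are needed alongside passive data and when they are not.

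**The concern.** Flare and score changes are defined from ePROs, and ePROs are also candidate predictors in the same models. Two routes to good performance then need no signal from the watch. A score change is partly predictable from the previous score through regression to the mean. A reported flare is likely to be predictable from reported pain or fatigue, and the models are meant for detection as well as prediction, with no stated exclusion of same-period items.

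The aims in the Introduction and Discussion need the digital contribution to be separable from the ePRO contribution. The AUC of one pooled model does not separate them. Comparing three algorithms on the same pool would not either. At stake is whether readers could take a good event model as evidence for the smartwatch when most or all of its accuracy comes from the questionnaires.

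**Working it through.** **The plan's own figures.** The article gives no performance target for the event models. Its only power statement concerns correlations, and the point does not depend on it; it is reproduced here because it supplies the sample size and effect sizes used in step 3. Inputs from Sample Size and Statistical Methods: "We aim to recruit 250 participants who have successfully completed the lead-in period" and "Assuming at least 75% of the participants complete the majority of the measures", so 0.75 × 250 = 187.5, taken as 188. Two-sided alpha of 0.05 is assumed, because the article states none. Power = Φ(atanh(r)·√(n − 3) − 1.96).
- r = 0.2: Φ(0.2027 × 13.60 − 1.96) = Φ(0.797) = 78.7%, close to the stated 80%.
- r = 0.3: Φ(0.3095 × 13.60 − 1.96) = Φ(2.25) = 98.8%, in line with the stated figure of over 90%.

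The documents give neither score reliabilities nor correlations between ePROs. All inputs below are therefore assumptions, shown as ranges.

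**1. Score change from the previous score alone.** Let two observed scores share an unchanging true score, with total variance 1 and reliability R. The correlation between change and previous score is then −√((1 − R)/2), although nothing has truly changed. The event is an observed worsening of more than 0.5 SD, and the only predictor is the previous score (1,000,000 simulated pairs).

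| R | correlation of change with previous score | AUC |
|---|---|---|
| 0.7 | −0.39 | 0.69 |
| 0.8 | −0.32 | 0.65 |
| 0.9 | −0.22 | 0.62 |

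**2. Flare from concurrent pain alone.** Pain and a flare score are bivariate normal with correlation ρ, and the event is the top 20% of the flare score. This stands in for a flare definition; the section itself describes a question on whether a flare is present now and when it began.

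| ρ | AUC |
|---|---|
| 0.5 | 0.75 |
| 0.6 | 0.80 |
| 0.7 | 0.85 |

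Steps 1 and 2 contain no digital variable, so its zero contribution holds by construction. They show how high an AUC can be without one.

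**3. Three predictor sets side by side.** Assumed: 188 participants over 12 weeks; a latent severity with person-level intraclass correlation 0.6 and week-to-week autoregression 0.4; an ePRO equal to the previous week's severity plus noise (SD 0.5); a digital measure correlated r with current severity; an event rate of about 20%; logistic models scored on independent data (60 repetitions).

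| r | ePRO only | digital only | both |
|---|---|---|---|
| 0 | 0.80 | 0.50 | 0.80 |
| 0.2 | 0.80 | 0.59 | 0.81 |
| 0.3 | 0.80 | 0.63 | 0.81 |

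The pooled column moves by about 0.01, whether the watch carries no signal or a signal of the size on which the study bases its power. The first two columns tell these cases apart, and they are the ones the article does not state for these models.

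**The case against.** The strongest reply is that this rests on a silence. The article says that models will be compared without saying how, and calls the variables potential factors. It does not rule out nested predictor sets. Feature sets, folds and metrics for secondary machine-learning models are commonly left to the analysis plan, which is not shown. That stands to this extent: no one can say that a benchmark has been excluded. But pooling ePROs with digital measures as candidate predictors of ePRO-defined events is stated in the article, and the point is about that stated choice and its fit to the aims.

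A reader might infer more: that the study cannot credit any good performance to the watch, or that no analysis isolates it. The documents do not support this.
- The flare classification is directed at digital measures and can speak to their stand-alone accuracy. It covers flare only and, with no ePRO comparator, does not give added value.
- The primary models relate passive measures to each ePRO and are untouched, so the proxy aim is not left without an analysis.
- Adherence, also listed as an event, is not circular in this way, and finding its predictors is a stated secondary objective.
- Earlier ePROs are legitimate predictors of later events.
- The article nowhere says that pooled performance will be credited to the watch.

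**Conclusion.** The point holds for the pooled models of flare and score changes, and only for those. Taken alone, their operating characteristics cannot show what the digital measures add to ePROs or could replace in them. The AUCs in the working show that the gap can be large, but their size rests wholly on assumed reliabilities, correlations and event definitions; they are illustrations and not forecasts for this study. It is an improvement that should be made to a secondary analysis. The primary analysis does not depend on it.

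**What to change.** For flare and score-change events, fit each planned model on three predictor sets: baseline plus earlier ePROs, baseline plus digital measures, and both. Use the same cross-validation folds for all three, split by participant so that one person's weeks never fall in both training and test data. Report the difference in AUC and Brier score between sets, with intervals. In detection models, exclude same-period ePRO items that define the event. Say in the text that the planned comparison of operating characteristics covers predictor sets as well as algorithms. The adherence models, the primary models and the digital flare classification can stay as they are. The cost is extra model runs on data already being collected; no new data are needed.
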